### Data Collection

All study procedures have been designed to be conducted remotely using telephone or video calls. At baseline, we will obtain information on sociodemographics, self-reported weight and height, and concurrent medical conditions and medications and data to assess stroke risk, frailty, and activities of daily living. At the end of the program, we will conduct a usability survey of all participants via phone calls to obtain information related to their experiences with the screening program and obtain further information on any adverse events while participating in the program (Multimedia Appendix 1). All GPs who have patients enrolled in the study will be invited to provide their feedback in a survey (Multimedia Appendix 2). All electronic data and documents related to participants and the project will be securely stored in the university computer drive accessible by authorized research team members only.

### Qualitative Evaluations

We have followed the Medical Research Council guidelines in designing the process evaluation [36]. Participants’ and GPs’ expectations and experiences of the screening program may be influenced by various contextual factors such as the participants’ social and cultural background and the GPs’ clinical practice resource and setting. Using a theoretical lens of critical realism [37], we will provide an explanatory analysis of the perceptions, experiences, and interactions with contextual factors that participants describe (ie, what works for whom and under what circumstances).

After participants have used the handheld ECG device for a minimum of 3 months, the research team will invite several participants in both groups (≥10 participants to achieve thematic saturation) to attend an in-depth semistructured interview to explore their views and feedback on the study. The semistructured interview will explore the participants’ feedback on their experiences with using the ECG device, use of the device for detecting irregular heart rhythm, participants’ perceptions of this remote screening method, and their access to health services generally (Multimedia Appendix 1). The invitation will be based on purposive sampling to obtain representative participants from a wide spectrum of demographic groups, that is, male or female, rural or urban, and frail or not frail.

GPs will be invited to a one-on-one in-depth interview, which will take approximately 20 to 30 minutes. The interviews will be audio recorded and transcribed by the research team. We plan to recruit at least eight GPs for this interview. A sample of 8 GPs is considered appropriate for the exploratory interviews [38]. However, more GPs will be recruited if thematic saturation is not achieved. The semistructured interviews will explore GPs’ views with respect to AF screening generally and in screening people aged ≥75 years particularly, their views of the patient-led self-screening in this research study, their knowledge of the use of mobile health devices (including handheld ECG devices) in clinical practice, and their views on using the handheld ECG device (ie, AliveCor Kardia) for AF screening in this study. In alignment with a critical realism [37] approach, the interview questions will explore GPs’ contextual factors and their interaction with patient participants and the research team with the aim of exploring GPs’ perception of their roles and barriers to and acceptability and enablers of this patient-led self-recording of a single-lead ECG program (Multimedia Appendix 2).

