
There is also a lack of information about the role and importance of patient empowerment with respect to the implementation of AF screening. The World Health Organization promotes patient empowerment (ie, training patients to perform and engage in health-related behaviors within their familiar setting) as it can potentially lead to positive health outcomes [24]. Patient empowerment can be incorporated in patient-led AF screening by training patients to self-record single-lead ECGs. However, patient empowerment has its limitations; that is, patients face automated ECG interpretation results that are often beyond their competence to understand and act upon, and it is impractical to have every ECG result individually and regularly checked by their clinicians. A centralized monitoring system is a feasible way of remotely monitoring a patient’s heart rhythm [25].

The processes of the screening program can vary in their actual implementation because of diverse contexts and participant characteristics (both patients and clinicians); for example, participants may be incapable of or not engage in performing self-recording of ECG, or they may not follow up with (or do not have access to) their clinician after a clinically significant abnormality is detected and notified. Process variations can affect outcomes. Therefore, it is important to evaluate the processes with the aim of better understanding why variations occur and how to improve the processes to achieve an effective intervention and identify contextually relevant strategies to scale up the screening program to benefit larger populations.

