### Outcome Measurements

The clinical outcomes include (1) new AF detected over 6 and 12 months and (2) appropriate use of anticoagulant therapy. The feasibility outcomes include (1) participant satisfaction that their heart rhythm was monitored in the past 6 months; (2) participant recruitment rate; (3) frequency of ECG transmission to the central monitor; (4) proportion of participants who complete the program; (5) proportion of dropouts (exit the program prematurely) and reasons; (6) actual costs of the screening program; (6) agreement between the ECG device’s automatic algorithm and clinician interpretation; (7) usability assessment; (8) participant acceptability and barriers to and enablers of implementation; and (9) impact of frailty on feasibility assessments and outcomes.

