The quantitative and qualitative analysis approach and methods are summarized in Textbox 1.

**Table 2 table2:** Process evaluation—implementation processes, mechanisms of impact, and contexts.

Process evaluation components	Descriptions	Methods and explanatory data	Anticipated outcomes
Implementation processes	Fidelity of implementation Participation in intervention Reach	Participant enrollment and characteristics, including socioeconomic status and frailty Participant engagement (number of self-recorded ECGs^a^) Clinician characteristics and involvement	Participants who are engaged with the intervention and satisfied with the program
Mechanisms of impact (how does intervention help adoption of AF^b^ self-screening)	Barriers and enablers	Participant engagement and satisfaction Participant survey and interview Clinician survey and interview	A feasible screening program
Context (how do factors external to the intervention affect uptake and implementation)	Participants’ overall health Community-dwelling environment Access to health care services General practitioner views and attitudes	Comorbidities, frailty, and functional status Participant demographic data, survey, and interview Clinician survey and interview	Identification of resources and implementation processes required for effective uptake and implementation of the screening program A contextualized feasible screening program

^a^ECG: electrocardiogram.

^b^AF: atrial fibrillation.

Description of analysis methods on outcome measures compared between the intervention group and waitlist control group.

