**Participant acceptability and barriers to and enablers of implementation**
In-depth one-on-one interview with participants (Multimedia Appendix 1) and general practitioners (Multimedia Appendix 2)Thematic analysis

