### Anticipated Challenges and Limitations

All study procedures have been designed to be conducted remotely by telephone or video interface to facilitate this study in the context of the COVID-19 pandemic. Therefore, the collection of baseline data and medical history relies on participants’ self-reported information. There is a potential for loss to follow-up in older patients who are frail; for example, participants do not record ECGs. We will attempt to minimize this by following up with patients when no ECG is received for 3 consecutive days. There may be a potential selection bias in this study based on the inclusion criteria. For example, this trial is limited to older people who can understand English and have a smartphone. These participants may come from higher socioeconomic communities and represent a more motivated cohort than the general population of older people.

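### The 3-month device-use condition keeps early stoppers out of the in-depth interviews, so the interview findings on barriers and acceptability are at risk of bias towards acceptability

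*Protocol article*

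**What the plan says.** Under Qualitative Evaluations, the article fixes when participants are approached and who they are: "After participants have used the handheld ECG device for a minimum of 3 months, the research team will invite several participants in both groups". The target number is "≥10 participants to achieve thematic saturation", and the purposive sample is to span "male or female, rural or urban, and frail or not frail". The section describes no exit interview and no stratum for engagement or completion.

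Textbox 1 gives the method for the acceptability, barriers and enablers outcome as "In-depth one-on-one interview with participants" and GPs, followed by thematic analysis. Table 2 draws on a wider set of sources for barriers and enablers: "Participant engagement and satisfaction Participant survey and interview Clinician survey and interview".

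The article expects some people to fail at or abandon recording. The Background warns that "participants may be incapable of or not engage in performing self-recording of ECG", and Anticipated Challenges and Limitations adds: "There is a potential for loss to follow-up in older patients who are frail". Separately, Outcome Measurements lists "proportion of dropouts (exit the program prematurely) and reasons" as a feasibility outcome, and Textbox 1 says this is kept on a log sheet.

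**The concern.** The interviews are meant to explain why the program works for some people and not for others. The people best placed to describe a prohibitive barrier are those who never got the device working or who gave up within weeks. As written, they never meet the condition for an invitation. Stratifying on frailty does not repair this, because the frail people interviewed will be those who were still using the device at 3 months.

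At stake is the second study objective, which covers acceptability, barriers, enablers and the influence of frailty on them, together with the process-evaluation aim of understanding barriers in depth. If saturation is judged only among continuing users, themes specific to early failure may be missing without anyone noticing. Any advice on scale-up drawn from the interviews would then describe the experience of people who coped.

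**Working it through.** The article gives no figure to reproduce on this point. The check sets the relevant parts side by side, then illustrates direction and scale under stated assumptions.

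**Which sources can reach someone who stops before 3 months?**

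| Source | Where | Reaches early stoppers? |
|---|---|---|
| In-depth participant interview | Qualitative Evaluations; Textbox 1 | No, as written |
| Dropout proportion and reasons (log sheet) | Outcome Measurements; Textbox 1 | Yes |
| Completion; ECG transmission frequency | Outcome Measurements; Textbox 1 | Yes |
| Contact after 3 consecutive days without an ECG, to find the cause | Intervention Group section | Yes |
| Satisfaction questionnaire at 6 months | Textbox 1 | Not restricted by the rule |
| Usability survey of all participants | Data Collection | Addressed to all, but at the end of the program |
| GP survey and interviews | Data Collection; Qualitative Evaluations | Indirectly |

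Only the first row is closed to early stoppers. It is also the only source that gives a participant's own in-depth account.

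**Illustration.** The article states neither an early-stop rate nor how common any barrier is. Assume:

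- d = share stopping before 3 months: 5%, 10%, 20% or 30%.
- b_s = 80% of early stoppers have a given barrier.
- b_c = 20% of continuing users have it (alternative: 40%).

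Prevalence among all users = d × b_s + (1 − d) × b_c. In the interview frame it is b_c.

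Example, d = 10%, b_c = 20%: 0.10 × 0.80 + 0.90 × 0.20 = 0.08 + 0.18 = 26%, against 20% in the frame, a gap of 6 points.

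If ten interviewees were drawn at random without the condition, the chance of at least one early stopper would be 1 − (1 − d)^10. At d = 10% this is 1 − 0.90^10 = 65%. With the condition it is 0.

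| d | People out of 200 | All users, b_c = 20% | Gap | All users, b_c = 40% | Gap | Chance of ≥1 stopper in 10, no condition |
|---|---|---|---|---|---|---|
| 5% | 10 | 23% | 3 points | 42% | 2 points | 40% |
| 10% | 20 | 26% | 6 points | 44% | 4 points | 65% |
| 20% | 40 | 32% | 12 points | 48% | 8 points | 89% |
| 30% | 60 | 38% | 18 points | 52% | 12 points | 97% |

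Thematic analysis does not estimate prevalence, and a purposive sample is not a random draw. The table therefore shows direction and rough scale only. The gap is positive whenever early stoppers meet a barrier more often than continuing users, and it grows with d.

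**The case against.** **Other sources cover early stoppers.** The interviews inform one of several feasibility outcomes. The primary feasibility outcome, satisfaction, comes from a questionnaire. Heavy early dropout would show directly in the completion, dropout and transmission figures. Staff ask about causes after 3 days of silence, the usability survey is addressed to everyone, and the Analysis section plans to triangulate quantitative and qualitative findings. This stands, and it sets the limit of the point: barriers behind early stopping are not wholly lost. It does not remove the point. The article does not say how detailed the log is, the 3-day contact is also meant to resolve the problem, and early leavers may be hard to reach for a survey at program end. Anticipated Strengths itself says that satisfaction scores do not give insight into experience and relies on interviews for that. Triangulation cannot supply accounts that were never collected.

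**The sentence may be about timing, not eligibility.** That reading is possible. No adherence threshold is set, so irregular recorders still using the device at 3 months can be invited. Even so, the article makes no provision for people who never reach 3 months.

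**The article is condensed.** The interview guide is in an appendix not shown, and exit procedures might exist elsewhere. The absence of a completion stratum would be weak evidence on its own. The 3-month condition, however, is printed in the text.

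**A stronger reading is tempting.** A reader might infer that the feasibility conclusion as a whole is biased, or that barriers will certainly be understated, most of all for frail people. The documents support neither. The other outcomes do not depend on this rule, frailty is both a sampling stratum and a planned subgroup, and continuing users also meet barriers.

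**Conclusion.** The point holds in a limited form. As written, the participant interviews leave out people who could not start or who stopped before 3 months, although the article itself names inability or failure to self-record as a reason for process variation. The interview-based findings on barriers and acceptability are therefore at risk of bias towards acceptability, on the assumption that early stoppers face more barriers than continuing users. Neither primary outcome is affected, and nor are the other feasibility outcomes.

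The size cannot be determined from the documents. Under the assumed values above, the understatement of a single barrier runs from 2 to 18 percentage points. This is an inexpensive improvement to one part of the process evaluation and does not threaten the trial's validity.

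**What to change.** In Qualitative Evaluations:

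1. Waive the 3-month minimum for participants who stop or withdraw earlier.
2. Add completion status (continuing or stopped early) to the purposive strata.
3. Use some of the planned interview slots for early stoppers who consent, at or soon after exit.
4. If none can be interviewed, limit the interview conclusions to users of at least 3 months and report them beside the logged dropout reasons.

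The cost is a line or two in the sampling plan and possibly an ethics notification. Early stoppers may decline more often, and a few slots for continuing users are given up. If slots are reallocated and not added, no extra staff are needed.

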### Outcome Measurements

The clinical outcomes include (1) new AF detected over 6 and 12 months and (2) appropriate use of anticoagulant therapy. The feasibility outcomes include (1) participant satisfaction that their heart rhythm was monitored in the past 6 months; (2) participant recruitment rate; (3) frequency of ECG transmission to the central monitor; (4) proportion of participants who complete the program; (5) proportion of dropouts (exit the program prematurely) and reasons; (6) actual costs of the screening program; (6) agreement between the ECG device’s automatic algorithm and clinician interpretation; (7) usability assessment; (8) participant acceptability and barriers to and enablers of implementation; and (9) impact of frailty on feasibility assessments and outcomes.

### Analysis

All analyses will be conducted according to the principle of intention-to-treat. Continuous variables will be presented as mean (SD) or median with IQR and categorical variables as frequency and percentage. The key outcomes, namely participant satisfaction in the AF screening program, usability of the screening program, and the incidence of new AF detected over 6 and 12 months, will be reported as frequency and percentages and will be compared between the intervention and control groups using the chi-square test. Comparisons between groups (intervention and control) for other outcomes will be assessed using the chi-square test or Fisher exact test for categorical variables and Student *t* test or Mann-Whitney test for continuous variables as appropriate. We will consider 2-tailed *P*<.05 as statistically significant. The agreement between the ECG device automatic algorithm and clinician interpretation will be evaluated using κ statistics. Subgroup analyses will be performed based on age, gender, and location. Subgroup analysis by frailty will be performed to examine the potential impact of frailty on the outcomes, feasibility, and acceptability of the program. The actual operational costs of delivering the project will be recorded and verified using invoices and receipts, including the costs of personnel involved in interpreting ECGs, which will be computed based on their hourly wages and the time they spent in their roles in this program. The resultant costs will be compared with the costs reported in the literature on the costs associated with the detection of AF in a similar older population. Missing data will be identified, and its causes will be described. Sensitivity analysis will be performed to examine the robustness of the findings [39].

Qualitative evaluation will be reported according to the COREQ (Consolidated Criteria for Reporting Qualitative Research) guidelines [40]. Interviews with patients and GPs will be thematically analyzed using an inductive approach [41]. Themes will be interpreted through the critical realism lens [37] and compared with the literature [42,43]. We will triangulate the quantitative and qualitative findings [44] from patient participants and GPs to acquire an in-depth understanding of the barriers to and enablers of implementing the screening program.

The process evaluation components [36], explanatory data, and anticipated outcomes are summarized in Table 2.

The quantitative and qualitative analysis approach and methods are summarized in Textbox 1.

**Table 2 table2:** Process evaluation—implementation processes, mechanisms of impact, and contexts.

Process evaluation components	Descriptions	Methods and explanatory data	Anticipated outcomes
Implementation processes	Fidelity of implementation Participation in intervention Reach	Participant enrollment and characteristics, including socioeconomic status and frailty Participant engagement (number of self-recorded ECGs^a^) Clinician characteristics and involvement	Participants who are engaged with the intervention and satisfied with the program
Mechanisms of impact (how does intervention help adoption of AF^b^ self-screening)	Barriers and enablers	Participant engagement and satisfaction Participant survey and interview Clinician survey and interview	A feasible screening program
Context (how do factors external to the intervention affect uptake and implementation)	Participants’ overall health Community-dwelling environment Access to health care services General practitioner views and attitudes	Comorbidities, frailty, and functional status Participant demographic data, survey, and interview Clinician survey and interview	Identification of resources and implementation processes required for effective uptake and implementation of the screening program A contextualized feasible screening program

^a^ECG: electrocardiogram.

^b^AF: atrial fibrillation.

Description of analysis methods on outcome measures compared between the intervention group and waitlist control group.

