**Methods:**

This is a nationwide randomized controlled implementation trial conducted via the internet and remotely among 200 community-dwelling adults aged ≥75 years with no known AF. Randomization will be performed in a 1:1 allocation ratio for the intervention versus control. Intervention group participants will be enrolled in the monitoring program at randomization. They will receive a handheld single-lead ECG device and training on the self-recording of ECGs on weekdays and submit their ECGs via their smartphones. The control group participants will receive usual care from their general practitioners for the initial 6 months and then commence the 6-month monitoring program. The ECGs will be reviewed centrally by trained personnel. Participants and their general practitioners will be notified of AF and other clinically significant ECG abnormalities.

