**Results:**

This study will establish the feasibility and effectiveness of implementing the intervention in this patient population. The primary clinical outcome is the AF detection rate, and the primary feasibility outcome is the patient satisfaction score. Other outcomes include appropriate use of anticoagulant therapy, participant recruitment rate, program engagement (eg, frequency of ECG transmission), agreement in ECG interpretation between the device automatic algorithm and clinicians, the proportion of participants who complete the trial and number of dropouts, and the impact of frailty on feasibility and outcomes. We will conduct a qualitative evaluation to examine the barriers to and acceptability and enablers of implementation. Ethics approval was obtained from the human research ethics committee at the University of Sydney (project number 2020/680). The results will be disseminated via conventional scientiﬁc forums, including peer-reviewed publications and presentations at national and international conferences.

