## Methods

### Study Design

This is a 2-arm, randomized, open-label, waitlist-controlled trial in community-dwelling people aged ≥75 years. We will also conduct a process evaluation of this study. Randomization in the ratio of 1:1 is stratified by participant frailty status (frail or nonfrail; Multimedia Appendix 1). Participant frailty was determined using the FRAIL (Fatigue, Resistance, Ambulation, Illnesses, and Loss of Weight) scale based on five components: *fatigue*, *resistance* (inability to climb stairs), *ambulation* (inability to walk a certain distance), *illness*, and *loss of weight* [28,29]. The intervention group will commence the monitoring program for 12 months upon enrollment. The control group will be waitlisted for the first 6 months and then commence the monitoring program in the subsequent 6 months. The steps involved for enrollment, randomization, intervention, control, and exit from the program are outlined in the study flowchart (Figure 2), and descriptions of the screening program are provided in the following sections.

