**New atrial fibrillation detected**
Frequency of occurrence and proportions at 6 months—via electrocardiogram collected at the central monitor (during intervention) and self-report and confirmation with medical records or electrocardiogram (during waitlist control period)

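### The planned 12-month between-arm test of new AF compares 12 with 6 months of monitoring, not screening with usual care, and Textbox 1 gives 6 months only

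*Protocol article*

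**What the plan says.** The abstract states: "The primary clinical outcome is the AF detection rate". It gives no time point. Outcome Measurements lists the first clinical outcome as "new AF detected over 6 and 12 months". The Analysis section names among the key outcomes "the incidence of new AF detected over 6 and 12 months, will be reported as frequency and percentages and will be compared"; its sentence says that these outcomes "will be compared between the intervention and control groups using the chi-square test", with a two-tailed 5% significance level.

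Study Design fixes what each arm receives. For the intervention arm: "The intervention group will commence the monitoring program for 12 months upon enrollment". For the control arm: "The control group will be waitlisted for the first 6 months and then commence the monitoring program in the subsequent 6 months". The abstract agrees; controls have "usual care from their general practitioners for the initial 6 months and then commence the 6-month monitoring program".

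Textbox 1, whose caption says it describes the outcomes compared between the intervention and waitlist control groups, gives a single time point for new AF: "Frequency of occurrence and proportions at 6 months". It also describes how AF is ascertained in controls while they are still on the waitlist. The Sample Size section uses detection rates of 10% and 1% and arrives at 200 participants, again without a time point.

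**The concern.** The first study objective is to compare AF ascertainment between arms. That is a comparison of screening with usual care only while controls are unmonitored. From month 6 every control is offered the program, so cumulative AF at month 12 contains 6 months of monitored detection in one arm and 12 in the other. The same chi-square test is specified for both time points, and nothing in the article says that the second answers a different question.

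What is at stake is interpretation. If screening works as the plan assumes, controls largely catch up between months 6 and 12 and the 12-month difference shrinks. A significant result at 6 months and a null one at 12 would then look contradictory, and the null could be read as evidence that screening has no effect or that its effect fades. Because the Analysis section and Textbox 1 differ on the time points, a reader cannot settle from the article alone how the 12-month figure is meant to be used.

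**Working it through.** **1. Reproduce the plan's figure.** Inputs from Sample Size and Study Design: p1 = 0.10, p2 = 0.01, two-sided α = 0.05, power 80%, 1:1 allocation.

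n per arm = [1.960·√(2·p̄(1−p̄)) + 0.842·√(p1(1−p1) + p2(1−p2))]² / (p1−p2)², with p̄ = 0.055.

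- First term: 1.960 × √0.10395 = 0.632.
- Second term: 0.842 × √0.0999 = 0.266.
- n = 0.898² / 0.0081 ≈ 99.5, so 100 per arm and 200 in total, which matches the plan.

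Power with 100 per arm is 80.2% by normal approximation and 85.4% by exact enumeration of the uncorrected chi-square test.

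**2. Which time point these rates fit.** A 1% control rate is plausible only while controls have no device, that is, up to month 6. I therefore read 10% and 1% as 6-month rates.

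**3. Expected control rate at month 12.** Assume that 6 months of monitoring finds the same 10% among controls not yet diagnosed: 0.01 + 0.99 × 0.10 = 0.109, or about 11%.

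**4. Expected intervention rate at month 12.** The article gives no yield for months 7 to 12. Call it r, a share of those still undiagnosed, so the rate is 0.10 + 0.90·r. The table takes r from 0 to 10%, with 100 per arm and no dropout.

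| r (assumed) | Intervention | Control | Difference (points) | Power, normal | Power, exact |
|---|---|---|---|---|---|
| 0% | 10.0% | 10.9% | −0.9 | 4.0% | 5.7% |
| 2% | 11.8% | 10.9% | +0.9 | 3.9% | 5.6% |
| 5% | 14.5% | 10.9% | +3.6 | 11.6% | 12.0% |
| 10% | 19.0% | 10.9% | +8.1 | 36.1% | 36.7% |

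With identical rates of 10.9% the exact rejection rate is 5.2%. The normal approximation counts one tail only, so it falls below 5% when the difference is near zero. The exact range is about 5% to 37%.

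**5. If the 10% was meant as a 12-month yield.** Take 5% in each half-year instead. The 12-month rates are 0.05 + 0.95 × 0.05 = 9.75% and 0.01 + 0.99 × 0.05 = 5.95%, with about 17% power by normal approximation; the 6-month test (5% against 1%) then has about 38%. The figures move, but the 12-month contrast is still one of monitoring duration.

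**6. Type I error of two tests.** The 6-month and cumulative 12-month outcomes are nested: anyone positive at 6 months is positive at 12. I simulated both tests with no difference between arms and 100 per arm. The chance of at least one rejection was 4.7% (1% yield per half-year), 7.1% (10% then 2%), 8.0% (10% then 5%) and 8.7% (10% then 10%).

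**The case against.** The strongest reply is that the article already contains the right comparison. Textbox 1 is its most specific statement of analysis methods, and it limits new AF to 6 months and describes control ascertainment during the waitlist period. That stands, and it narrows the point to the broader sentences in Outcome Measurements and Analysis, which were not brought into line.

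A second reply is that the 12-month contrast is a valid randomised comparison. The Introduction names longer self-monitoring as a gap in the evidence, and 12 against 6 months of monitoring bears on it. That also stands. The fault is the missing label and the low power, not an invalid test.

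Three stronger readings are tempting, but the documents do not support them.

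- A reader might infer that the trial's main comparison is compromised. It is not: the 6-month contrast, its sample size and its data collection are unaffected.
- A reader might infer that either time point could be declared primary after the results are seen. Nothing in the article calls 12-month AF primary. The 1% control rate points to 6 months, as do the 6-month assessments of satisfaction and anticoagulant use. A fuller plan that is not shown may name the time point.
- A reader might apply 1 − 0.95² = 9.75% as the type I error of two tests. That needs independent outcomes. These are nested, and simulation gives about 5% to 9%. The two tests also address different questions once the second is read correctly.

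**Conclusion.** The concern holds in a limited form. Outcome Measurements and Analysis commit to a 12-month intervention-versus-control test that cannot be read as screening against usual care, and they disagree with Textbox 1. This is a rule the article states, not a detail left to another document.

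The conclusion about what is being compared follows from the design and needs no assumption. The power figures do need some: 10% and 1% taken as 6-month rates, the same monitoring yield in controls once they start, no dropout, and a yield in months 7 to 12 that the article does not give. Within the 10% to 19% range assumed for the intervention arm, a null 12-month result is more likely than not even if screening performs as planned. Severity: should be fixed.

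**What to change.** In Outcome Measurements and Analysis, follow Textbox 1. Name AF detected by 6 months after randomisation, before controls start monitoring, as the primary clinical outcome. State that this is the time point of the sample size calculation and of the test of screening against usual care.

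Report 12-month AF descriptively by arm, or as a secondary comparison explicitly labelled 12 versus 6 months of monitoring, and say that it is not evidence on screening against usual care.

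The cost is one or two sentences, with no new data, participants or procedures. What is given up is reading the 12-month P value as a test of screening.
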